### Randomization and blinding

After participants are enrolled in the study and have completed baseline assessments, an independent technician will generate a randomization sequence. The random sequence will be created using a random number generator (IBM SPSS Statistics V.25.0 software; IBM). The random allocation sequence will be sent to the therapists in sequentially numbered opaque envelopes [18]. The therapists will open the envelopes in sequence and assign participants, who meet the inclusion criteria, to the corresponding group. While the study assessors will be blinded to the group allocation of the participants, neither the therapists nor the participants can be blinded due to the nature of the interventions. The continued use of sham NMES for participants can play a key role in minimizing performance bias. Sham NMES provides a control condition that mimics the setup and experience of the intervention without delivering therapeutic electrical stimulation. This approach enables us to isolate the effects of active NMES on clinical outcomes (such as pain, proprioception, and muscle activation) by ensuring that any observed improvements are not simply due to placebo effects, psychological factors, or participants’ awareness of receiving NMES treatment. To minimize bias, assessors, data managers, and analysts will remain blinded to group assignments during outcome assessments and data analysis. The study design and trial flowchart are illustrated in Figs 1 and 2.

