## Methods

### Study design

This study will be a single-center, prospective, randomized, sham-controlled trial conducted at the outpatient rehabilitation center of the Sir Run Run Shaw Hospital, affiliated with Zhejiang University School of Medicine. A total of 52 participants will be recruited and randomly assigned in a 1:1 ratio to one of the following two groups: (a) experimental group, receiving NMES superimposed on CSE to enhance activity levels; (b) control group, receiving the same CSE with sham NMES. All participants in both groups will undergo 20-minute sessions, three times per week, for a 6-week intervention period. The study outcomes will be evaluated before (t0), six weeks after initiating interventions(t1), and six months (t2) after starting the protocol. The study protocol follows the standards described in the “Standard Protocol Items: Recommendations for Interventional Trials” guideline (S1 File) [12].

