Participants in the experimental group will receive NMES using the EN-Stim4 device (ENRAF-NONIUS B.V., Bunnik, Netherlands) applied to the bilateral LM and TrA/internal oblique muscles(IO) (Fig 3). For the NMES configuration, the abdominal electrodes will be positioned as follows: the cathode (negative electrode) will be placed 1 cm above the iliac crest along the mid-axillary line, while the anode (positive electrode) will be located 2 cm medial to the anterior superior iliac spine. For the lumbar electrodes, the cathode (negative electrode) will be positioned approximately 2 cm lateral to the spinous processes of L4 and L5, with the anode (positive electrode) placed at a distance from the cathode to ensure optimal current flow through the lumbar region [21]. The electrodes used will be 5 cm × 5 cm surface hydrogel electrodes. The NMES used in this study will be applied with the following parameters: a frequency of 50 Hz, a 200 μs pulse width, and a biphasic symmetric waveform, which is effective for recruiting both superficial and deep muscle fibers [22]. The stimulation will follow a contraction-relaxation cycle comprising an ascent phase of 1 second, a contraction phase of 4 seconds, a descent phase of 1 second, and a resting phase of 6 seconds, lasting a total of 20 minutes. The current intensity will be adjusted to achieve the maximum muscle contraction without causing discomfort, such as burning sensations or severe cramping pain. NMES intensity is adjusted weekly based on participant feedback and tolerability, as well as to match improvements in muscle strength and activation capacity. Intensity increases are guided by the participant’s perception of a “strong but comfortable” stimulation level and monitored through visible muscle contractions. CSE will be performed during the contraction phase of the electrical stimulation and will cease during the resting phase. These exercises will include abdominal activation training in supine, prone, and quadruped positions, as well as bridge exercises and planks (Table 1). Each session will consist of 8 different exercises, performing 1 set of 10 repetitions per exercise, lasting 20 minutes per session, once per day, 3 days per week [23]. Participants in the control group will undergo the same CSE and NMES treatment, but the NMES current intensity will be set to a level that only elicits minimal sensory perception in the participants (generally below 5 mA). This ensures that while the participants experience the same treatment protocol, they do not receive the therapeutic benefits of NMES, allowing for an effective comparison between the experimental and control groups.

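### The protocol says participants cannot be blinded, yet claims that the sham excludes placebo effects and awareness of treatment; one of the two statements has to go

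*Protocol article*

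**What the plan says.** The Study design section calls the study a "single-center, prospective, randomized, sham-controlled trial". The Randomization and blinding section then makes four statements that bear on this point:

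- On participants and therapists: "neither the therapists nor the participants can be blinded due to the nature of the interventions".
- On the sham, in a modest form: "The continued use of sham NMES for participants can play a key role in minimizing performance bias".
- On the sham, in a strong form: it isolates the effect of active NMES on clinical outcomes "by ensuring that any observed improvements are not simply due to placebo effects, psychological factors, or participants’ awareness of receiving NMES treatment". The examples given there are pain, proprioception and muscle activation; disability is not among them.
- On everyone else: "assessors, data managers, and analysts will remain blinded to group assignments during outcome assessments and data analysis".

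Under Intervention measures, active current is raised to the strongest contraction that causes no discomfort. It is adjusted weekly, guided by how strong the participant feels it to be, and checked by watching the muscle contract. In the control arm, "the NMES current intensity will be set to a level that only elicits minimal sensory perception in the participants (generally below 5 mA").

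Under Secondary outcome measures, pain is self-reported on the VAS and the ODI is completed by the participant. The primary outcomes are sEMG muscle activity and activation timing.

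**The concern.** A sham removes expectation and awareness as explanations only if participants do not know which stimulation they receive. One paragraph says they cannot be kept unaware and also says that the sham ensures the benefit that only unawareness provides. If the first statement is right, the strong claim for the sham is wrong. If the strong claim is right, the non-blinding statement is wrong.

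At stake is what a group difference in pain or disability may be said to show. The Introduction's hypothesis includes less pain and better function with NMES. For VAS and ODI the participant is in effect the assessor, so blinding the assessors, data managers and analysts does not protect these outcomes. A reader who relies on the strong claim would attribute a VAS difference to the current. A reader who relies on the non-blinding sentence would see an unblinded self-report.

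**Working it through.** The protocol gives no figure on this point, so there is none to reproduce. The check is mainly a comparison of the text with itself.

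**Step 1. Can both statements hold?** Excluding participants' awareness of treatment as an explanation requires that they be unaware of their arm. The non-blinding sentence denies this without qualification. No other section reconciles the two.

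**Step 2. Does the modest claim fail too?** No. Both arms get the same exercises, device and session schedule. The sham therefore equalises setup, contact time and attention whether or not participants know their arm. That is enough for the sentence on performance bias, which says only that the sham can help to minimise it.

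**Step 3. Could participants be unaware in practice?** The Intervention measures section sets these conditions:

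| Feature | Active arm | Control arm |
|---|---|---|
| Intensity target | Strongest contraction without discomfort | Minimal sensation, generally below 5 mA |
| What is felt and seen | Strong stimulation, visible contraction | Barely felt |
| Weekly adjustment | Described | Not described |

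The first two rows give a participant good reason to guess. A participant with no comparison might still not know, so the settings do not prove unblinding. They do show that unawareness cannot be taken for granted. The consent form is not shown, so what participants are told about the two arms is unknown.

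**Step 4. Which outcomes are exposed?** Chiefly VAS and ODI, because the participant supplies the value. Pain is named in the attribution sentence. Disability is not, but it is exposed for the same reason. Measures that depend on voluntary effort or attention may also be affected, such as the rapid lifting task behind activation timing and the joint repositioning test. They are recorded by instrument or by blinded assessors, so the exposure is less direct.

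**Step 5. Illustration of size, resting on assumptions.** Suppose NMES has no true effect, but knowledge of the arm shifts the group difference by *b* SD. The value of *b* is assumed; nothing in the protocol fixes it. For a two-sided two-sample t-test with *n* per arm:

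- df = 2*n* − 2
- noncentrality λ = *b* × √(*n*/2)
- P(significant) = 1 − F(t₀.₉₇₅; df, λ) + F(−t₀.₉₇₅; df, λ), where F is the noncentral t distribution function

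Inputs from the protocol are 26 per arm and 20% dropout (Sample size calculation) and a two-sided level of 0.05 (Statistical analysis). After dropout, 26 × 0.8 = 20.8, or about 21 per arm.

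| Assumed shift *b* | λ, n = 26 | P, n = 26 | λ, n = 21 | P, n = 21 |
|---|---|---|---|---|
| 0 | 0 | 0.050 | 0 | 0.050 |
| 0.2 | 0.72 | 0.109 | 0.65 | 0.097 |
| 0.3 | 1.08 | 0.186 | 0.97 | 0.158 |
| 0.5 | 1.80 | 0.424 | 1.62 | 0.353 |

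The plan specifies a mixed ANOVA with Bonferroni-adjusted post hoc tests, not this test. The table shows how such a bias would act, not the error rate of the planned analysis.

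**The case against.** The best defence is that the sham does useful work whether or not participants are blinded, and that the wording is hedged: improvements are said to be not *simply* due to placebo. The first part stands. A reader might infer from the non-blinding sentence that the sham has no controlling function at all; the document does not support that, because setup, contact and exercise are matched. The second part does not rescue the strong claim. The sentence speaks of ensuring, and it names participants' awareness explicitly.

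A second defence is that the primary outcomes are instrumental sEMG measures taken with assessors blinded, while VAS and ODI are secondary. This also stands. A reader might infer that the contradiction undermines the trial's main result, or that the protocol promises to isolate an effect on disability. The first goes further than the text allows, and the attribution sentence does not mention disability.

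Third, the non-blinding sentence may be a drafting slip and participants may in fact be kept unaware. That is possible. A reader might equally conclude that participants will certainly know their arm. Neither can be settled without the consent text, and in either case one of the two sentences needs to change.

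Finally, a treatment-guess question has known weaknesses. Asked just before VAS and ODI it could prime the answers, and after six weeks a guess partly reflects perceived benefit. Both points stand and limit how the question should be used.

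**Conclusion.** The point holds as an internal contradiction: as written, the protocol claims a property of the sham that its own blinding statement denies. The sentence on minimising performance bias may stay. The sentence that claims to exclude placebo effects and awareness may not stand beside the non-blinding statement.

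The consequence is limited but real. It decides whether a difference in VAS or ODI may be attributed to the stimulation itself or must be reported as open to expectation bias. Confidence is high for the conflict in wording. It does not extend to whether participants will actually know their arm.

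No size of bias follows from the document. The ranges of 19 to 42% (26 per arm) and 16 to 35% (21 per arm) rest on an assumed shift of 0.3 to 0.5 SD, no true effect and a simple t-test. They should not be cited as the trial's false-positive rate.

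**What to change.** State one blinding status for participants and make the claim for the sham match it.

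- **(a) If participants are not told their arm:** correct the non-blinding sentence so that it covers therapists only, and describe the sham as an attempt at participant blinding rather than a guarantee. Add one question at t1, after the outcome measurements, on which stimulation the participant believes they received. Report the answers descriptively by arm, and note that guesses also reflect perceived benefit.
- **(b) If participants will know their arm:** delete the claim about placebo effects, psychological factors and awareness. Keep the sentence on performance bias. Report VAS and ODI as unblinded self-reported outcomes open to expectation bias.

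The cost is a few reworded sentences and a weaker attribution claim. Under (a) there is also one added question at an existing visit, which may need an ethics notification. Neither option changes the stimulation, the exercise programme or the sample size.

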**Fig 1 pone.0322398.g001:**
[figure not shown]
Study design schedule. CSE, core stability exercise; NMES, Neuromuscular electrical stimulation; TrA, transverse abdominis; EO, external oblique; IO, internal oblique; LM, lumbar multifidus; ES, erector spinae.

**Fig 2 pone.0322398.g002:**
[figure not shown]
Flow diagram of the study. CSE, core stability exercise; NMES, Neuromuscular electrical stimulation; VAS, Visual Analog Scale; ODI, Oswestry Disability Index; JRE, joint repositioning error; RUSI, real-time ultrasound image.

### Strategies to increase treatment adherence

Assessors will maintain regular communication with participants throughout the study to monitor their progress and address any discomfort or challenges. Participants will be encouraged to promptly report any increase in pain, discomfort, or difficulty in performing exercises or tolerating NMES. If any issues arise, the research team will assess the individual’s condition and make necessary adjustments to the treatment protocol. These adjustments may include modifying the intensity or duration of NMES, altering the difficulty level of exercises, or providing alternative movements to ensure proper execution while minimizing pain. If NMES settings prove intolerable, parameters such as frequency, intensity, or pulse duration may be adjusted to improve comfort without compromising effectiveness. Additionally, the progression of CSE will be personalized, allowing flexibility in exercise advancement based on each participant’s physical capability. To enhance adherence, assessors will offer continuous guidance, encouragement, and regular check-ins, reinforcing motivation and addressing concerns in real time. By implementing these strategies, the study aims to optimize participant engagement, ensure a tolerable and effective intervention, and maximize the benefits of the treatment protocol.

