Measurement of Muscle Activation Timing: To assess the latency of trunk muscle activation, participants will perform a lifting task while standing quietly, which introduces an inherent perturbation to the trunk and requires anticipatory postural adjustments (APA) [24]. The electrode placements will be the same as those used for muscle activity monitoring. Participants will stand with their elbows fully extended at 0°, shoulders flexed at 40°, and grasp the handles of a 5 kg box placed on a table in front of them. They will be instructed to lift the box to a shoulder flexion angle of 90° as quickly as possible and maintain this position for 3 seconds. After familiarizing themselves with the movement, participants will complete three repetitions of the lifting task, with a 1-minute interval between each trial. If any trunk or pelvic motion is observed during the trial, that attempt will be considered a failure. For sEMG processing, the procedures for manually selecting activation timings are as follows: Raw sEMG signals will first be filtered using a band-pass filter (20–450 Hz) to remove noise and artifacts. The baseline sEMG levels will be defined by calculating the RMS value of a 500 ms resting period before the onset of muscle activation. Muscle activation will be identified when the sEMG signal exceeds 3 standard deviations (SD) above the baseline RMS for a minimum duration of 50 ms. If necessary, trained assessors will visually inspect and manually adjust the activation timing to account for signal variations and artifacts, ensuring consistency across trials. The relative difference in onset activation times between each trunk muscle and the anterior deltoid will be calculated using the following formula: Relative Onset Activation Time Difference = Onset Activation Time of Trunk Muscle - Onset Activation Time of Anterior Deltoid (ms) [26]. A positive value indicates that the target trunk muscle is activated after the anterior deltoid. The average onset time from the three repetitions for each trunk muscle will be computed and used as the basis for data analysis.

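### Assessors described as blinded are also given in-treatment contact about discomfort and adherence, which is likely to disclose the arm before they may hand-correct a primary sEMG onset time

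*Protocol article*

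**What the plan says.** **Blinding.** The section Randomization and blinding makes the claim twice. First: "While the study assessors will be blinded to the group allocation of the participants, neither the therapists nor the participants can be blinded". Then: "assessors, data managers, and analysts will remain blinded to group assignments during outcome assessments and data analysis".

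**Contact during treatment.** Strategies to increase treatment adherence gives the same job title a continuing role with participants: "Assessors will maintain regular communication with participants throughout the study to monitor their progress and address any discomfort or challenges". The next sentence widens what will be talked about: "Participants will be encouraged to promptly report any increase in pain, discomfort, or difficulty in performing exercises or tolerating NMES". The section later adds: "To enhance adherence, assessors will offer continuous guidance, encouragement, and regular check-ins, reinforcing motivation and addressing concerns in real time". Where a problem arises, it is the research team, not expressly the assessors, that will "make necessary adjustments to the treatment protocol".

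**Contrast between arms.** Intervention measures sets active current to the strongest contraction the participant can take without discomfort and reviews intensity weekly. Sham current is set so that it is only just felt, generally below 5 mA.

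**Measurement.** The abstract and Primary outcome measures make muscle activation timing one of two primary sEMG measures. Onset is found by a threshold rule: signal more than 3 SD above baseline RMS for at least 50 ms. Then, if necessary, "trained assessors will visually inspect and manually adjust the activation timing to account for signal variations and artifacts".

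**The concern.** The protocol says that neither participants nor therapists can be blinded. Protection against detection bias therefore rests on those who measure, manage and analyse the data, and assessors are the only ones of these who meet the participant. A regular conversation about discomfort, with someone who knows or can feel which treatment they receive, is a direct route by which an assessor learns the arm.

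This matters most where the assessor has discretion over a number. Onset timing is such a place: a rule fixes the value and an assessor may then move it. An assessor who knows the arm and the study hypothesis could resolve doubtful traces differently in the two groups without intending to. A difference produced in that way cannot be told apart from a treatment effect, and lost blinding cannot be restored at analysis.

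**Working it through.** The protocol gives no figure on this point, so the check is a comparison of its sections.

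1. **Is it the same role?** The blinding section, the adherence section and the activation-timing text all use the word assessors. The article defines no separate adherence staff and does not say that the people making contact are barred from outcome measurement. It does not state outright that they are the same individuals either. On a plain reading they are.

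2. **Does the contact come before the exposed measurements?** Baseline (t0) is completed before randomization, so t0 values cannot be affected if they are read at that time. Treatment runs 3 sessions × 6 weeks = 18 sessions. Assessments at t1 (six weeks) and t2 (six months) follow. Contact throughout the study therefore precedes both post-treatment readings.

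3. **Would the contact disclose the arm?** The arms differ in the very thing participants are asked to report. Complaints about strong contractions, or mention of a rise in intensity, point to active NMES. Remarks that the current can hardly be felt point to sham. No instruction asks participants to keep this from assessors. Disclosure is an inference from these sections together; the text does not say that assessors are told the allocation.

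4. **Which primary outcome is reachable?** Onset time is, through the manual adjustment, which is conditional and sits on top of the threshold rule. Signal variations and artifacts are the only reasons named for using it. RMS amplitude is computed on a fixed window (5 s recorded, first and last second dropped, leaving 3 s) with no manual step stated.

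5. **How large could the effect be?** The document cannot answer this. As an illustration only, assume no true effect, a two-sided 5% two-group t-test, and a mean bias of b SD across one whole arm. The noncentrality is b × √(n₁n₂/(n₁+n₂)). With 26 per arm the multiplier is √(676/52) = √13 = 3.606, with 50 degrees of freedom and a critical value of 2.009. For b = 0.2 the noncentrality is 0.721, and the rejection probability from the noncentral t is 0.109. The second set of group sizes uses the protocol's minimum of 43 participants.

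| Assumed shift b | Rejection, 26/26 | Rejection, 21/22 |
|---|---|---|
| 0.05 SD | 5.4% | 5.3% |
| 0.1 SD | 6.4% | 6.2% |
| 0.2 SD | 10.9% | 9.8% |
| 0.3 SD | 18.6% | 16.1% |
| 0.5 SD | 42.4% | 36.0% |

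The shifts are chosen, not derived. The test is simpler than the planned mixed ANOVA. Each shift is an arm-wide mean that would have to arise from occasional overrides within three-trial averages. The table shows only that the consequence runs from trivial to serious depending on a quantity nobody can read from the protocol.

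**The case against.** The best defence is that nothing in the text gives assessors the allocation. Changes to stimulation settings belong to the research team, and the supervising therapist evaluates pain, function and motor performance at each session, so assessors may only be offering general support. The blinding section also says that sham mimics the set-up and guards against effects of participants' awareness, so participants may know less than the flat statement that they cannot be blinded implies. Onset is determined by a rule, and adjustment is the exception.

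Much of this stands as a limit on wording. Disclosure is likely, not certain. The protocol is inconsistent about what participants know. The manual step is conditional. None of it removes the conflict: addressing discomfort and concerns is assigned to assessors by name, and the difference in stimulation can be felt whatever participants have been told. Nor is this detail that an article leaves to the full protocol; it is an affirmative assignment that works against a stated safeguard.

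A reader might infer more, and the documents do not support it:

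- **That assessor blinding is the only blinding claimed.** Data managers and analysts are also said to be blinded, and Data collection and management repeats this for the data managers.
- **That assessors are shown to take every operator-dependent measurement.** No operator is named for ultrasound, and repositioning error is measured by an examiner. Pain is self-reported and participants select their own ODI responses, so assessor blinding would not remove bias that participants themselves bring to those two scales.
- **That assessors set or change NMES.** The text does not say so.
- **That both primary measures are open to manual influence.** Only onset timing is.
- **That bias must favour the hypothesis.** That is plausible but assumed.

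**Conclusion.** The concern holds in this form: the protocol promises blinded assessors and then gives assessors in-treatment contact that is likely to disclose the arm, without separating the two roles, and it lets assessors override a primary outcome value. Detection bias can therefore enter the onset-time outcome at t1 and t2. This rests on two readings: that the term assessors means the same staff throughout, and that talk of discomfort or tolerability will often touch on stimulation strength. Neither is stated outright, but the text offers nothing against the first, and the contrast between arms supports the second.

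The size of the bias is unknown. The illustrative rejection rates, from just above 5% to about 42%, depend wholly on the assumed shift and should not be quoted as an estimate. The case for changing the plan rests on the contradiction, on its reach into a primary outcome, and on the fact that blinding once lost cannot be recovered.

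**What to change.** 1. In Strategies to increase treatment adherence, replace assessors with the treating therapists for tolerability, encouragement and check-in contact. They are already unblinded, see participants three times a week, and evaluate them at each session.
2. State that outcome assessors meet participants only at t0, t1 and t2, have no part in adherence contact, and that participants are asked not to discuss stimulation with them.
3. In the activation-timing text, state that any manual onset adjustment is made from coded recordings with the arm hidden. Log each override, keeping the threshold-based value beside the adjusted one.

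The cost is minor: an existing task moves to staff already in contact with participants, recordings are given coded names, and a short log is kept. No extra visit is needed. Therapists take on somewhat more contact, including any that continues after the six-week treatment period. The change should be made while participants are still being treated and assessed.
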